### EMA and Stop-Cannabis App Tools

#### Ecological Momentary Assessment

The EMA was designed as an app for mobile phones. This application allows several daily self-assessments (e.g., five times a day for 2 weeks at different times of the study/monthly). Data are collected in response to a signal from the EMA app that occurs at various times of the day. The app has been programed to send signals (i) a fixed number of times per day at predetermined times (e.g., at bedtime) and (ii) at random (with a balance between week, weekends, and holidays, with different time intervals in daytime). Participants are also asked to complete self-assessment immediately following substance use.

The same questions are presented regardless of assessment type. There are seven questions in total:
Information relating to substance use:
○Daily use of each substance in list.○Level of withdrawal symptoms during participants’ most recent period of abstinence from 0 (not at all) to 5 (severe).○Level of craving from 0 (no urge) to 5 (extreme urge).Information relating to psychopathology:
○Level of negative affect rate using a brief version of the Positive and Negative momentary Affect Scale (PANAS) (48) adapted for EMA (32). Participants provide ratings of the extent to which they felt each emotion on a 1–5 point Likert-type scale.○Main psychiatric symptoms.Information relating to environment:
○Stressful events.○Activities: physical activity, planned activity, lone activity, social activity with peers, family activity, and online activity.

Participants will be trained on EMA use during the week prior to hospital discharge. They will be asked to respond to any signals within 1 h if possible. Consistent with other EMA protocols, participants will complete 2 days of practice data (not used for analyses), after which they will receive feedback on adequate use and compliance. Participants will then be invited to complete EMA assessments for 2 weeks, as this timeframe appears sufficient to monitor substance use (45). To limit attrition, participants will be paid 30€ for completing the baseline assessment and 10€ for each week of complete EMA data, up to a maximum possible payment of 60€ over 1 year.

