#### The Stop-Cannabis App

Launched in 2013, Stop-Cannabis is available free on iOS and Android. It has been continuously updated and improved over the past 3 years, in response to users’ suggestions. When people use the app for the first time, they are asked to document their objectives and choose a quitting date. The app has several modules. First, it allows users to assess their cannabis usage profile (including motivations for use and severity of cannabis use) *via* different assessments (49). Users then receive an individually tailored feedback message that includes links to online psychoeducation and complementary resources. Second, motivational messages are regularly delivered using push-notification technology at different stages of the quitting process, on the basis of updated information regarding current substance use, the selected quitting date, and exposure to situations associated with a high risk of relapse documented by high levels of craving or irritability. Third, the app includes messages on how to cope with craving symptoms or emotional difficulties to enhance participants’ insight into contextual factors for substance use. Fourth, positive reinforcers, such as the number of days since quitting the substance and the amount of money saved, are displayed on the main screen and can be personalized (Figure 1). Fifth, a discussion forum called “The Tribe,” moderated by a psychologist, is available for all users to encourage discussion, mutual support, and information sharing. Sixth, the app includes direct access to a website^2^ for additional information about substance use and online motivational interviewing training.

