**Ecological momentary intervention “Stop-Cannabis.”**
*Notes*: screenshots of the welcome page, the Feedback page, and the main screen with the benefits of change. Adapted from: Monney et al. (39).

The app will automatically monitor the number of times each participant opens the app and records the number of times participants looked at or used each element. A Unique Device Identifier (UDI) is used to connect the participants’ device to the study database and will be replaced in the data set with a random ID for anonymity. After study completion, the UDIs will be automatically deleted from users’ devices. The app will be available for participants in the intervention group for 12 months. After this period, the app will automatically stop data collection. However, participants are free to use the app for as long as they want.

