##### Primary Outcomes

The first parameter is whether the level of adherence and the acceptability of the EMA and the Stop-Cannabis app are satisfactory in this sample. Acceptability will be assessed by measuring the dropout rate after 6 and 12 months, and usability and satisfaction *via* questionnaire in all participants and *via* face-to-face interviews with a subgroup of 10 participants. Compliance will be assessed *via* mean percentage of random prompts and predetermined assessments completed per participant. The second parameter is whether information collected using EMA *via* a mobile app is valid and reliable. Information obtained by EMA tools using the mobile app will be compared to those collected by traditional paper–pencil and clinical interview methods during the initial and follow-up assessments using correlations analysis.

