##### Secondary Outcomes

(1)The prevalence of SUDs among adolescent inpatients will be assessed.(2)The clinical and psychosocial characteristics of participants with and without SUDs at baseline, including history of adverse childhood experiences, comorbid psychiatric diagnoses, and the level of functional impairment, will be compared.(3)The risk of developing SUDs among non-SUD adolescents during a 1-year follow-up period following hospital discharge will be investigated.(4)The proportion of inpatient adolescents with non-cannabis substance use at baseline whose SUDs persist at 1 year will be estimated.(5)We will explore how psychiatric symptoms could affect the pattern of substance use among SUDs participants.(6)We will assess whether specific patterns of Stop-Cannabis app use is associated with substance use outcomes at 1-year follow-up.

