##### Secondary Outcomes

(1)The number of inpatients with SUDs will be compared with the total number of adolescents admitted to the Department during the inclusion period.(2)Descriptive analyses of clinical and psychosocial variables will be conducted. Chi-square will be used to compare categorical variables, and Student’s *t*-test for continuous variables. A difference of *p* < 0.05 will be considered statistically significant.(3)Univariate logistic regression analyses will be performed to determine whether clinical features (as independent variables) predict the onset of SUDs at 1 year (as dependent variable) in the non-SUD control group and persistence or cessation in the SUD group. Possible mediators of this relation will be examined using the four-step approach proposed by Baron and Kenny (65), followed by a Sobel–Goodman test. In particular, we will test the mediation effect of the baseline impulsivity score, the baseline level of sensation-seeking (subscales of the UPPS-P score), and the baseline level of mood lability (ARI total score) on the relationship between psychopathology and SUDs.(4)Comparable analyses would be conducted to determine the clinical and psychosocial risk factors for the persistence of SUDs among those with non-cannabis substance use at baseline.(5)Specific analyses based on mixed-effect models (a random effect for participants and fixed effects for time) will be performed to examine the interplay between the pattern of substance use, psychiatric symptoms, and contextual stressors for treating EMA data [as in Ref. (45, 66)]. In line with previous recommendations, data will be studied at the daily level (with average ratings), at the concurrent momentary level, and at the prospective level using both linear and non-linear modeling (32). These analyses will be performed and presented separately between those with cannabis use disorder and the other participants to prevent any interference due to the use of the Stop-Cannabis app.(6)Correlational analyses will be carried out to examine the association between the level of app use (EMA or Stop-Cannabis) (i.e., mean percentage of random prompts, mean percentage of days assessment completed) and participant’s clinical outcome at follow-up (i.e., frequency of substance use and level of functional impairment at 1 year).

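### Stop-Cannabis use is defined by EMA prompt and assessment completion, and the app's own usage log is linked to no outcome or analysis

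*Protocol article*

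**What the plan says.** All references are to the protocol article.

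- **Objectives.** The primary objective covers feasibility, acceptability and use of Stop-Cannabis alongside the EMA tool. Secondary objective (6) concerns Stop-Cannabis use and substance use at 1 year.
- **Outcomes, Primary Outcomes.** Of the two questions posed here, one asks "whether the level of adherence and the acceptability of the EMA and the Stop-Cannabis app are satisfactory in this sample". Compliance is then given one metric: "mean percentage of random prompts and predetermined assessments completed per participant".
- **Outcomes, Secondary Outcomes (6).** The question is "whether specific patterns of Stop-Cannabis app use is associated with substance use outcomes at 1-year follow-up".
- **Statistical Methods, Secondary Outcomes (6).** The exposure to be correlated with clinical outcome is "the level of app use (EMA or Stop-Cannabis) (i.e., mean percentage of random prompts, mean percentage of days assessment completed".
- **Ecological Momentary Assessment.** "Data are collected in response to a signal from the EMA app that occurs at various times of the day"; these signals are sent at fixed times and at random.
- **The Stop-Cannabis App.** The app offers modules, a forum and messages: "motivational messages are regularly delivered using push-notification technology at different stages of the quitting process". In the text below Figure 1, the app is to "monitor the number of times each participant opens the app and records the number of times participants looked at or used each element", with data collection running for 12 months.

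**The concern.** A completion percentage needs a denominator: a known number of prompts or assessments that were due. The article describes such a schedule for EMA and none for Stop-Cannabis. Yet the exposure definition in analysis (6) is introduced by i.e., so it reads as a definition and not an example, and it is applied to both apps.

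Two things are at stake. First, objective 6 would be answered with an EMA compliance figure. According to the Abstract, every participant with a confirmed SUD is offered EMA, and Stop-Cannabis is added only if required. The figure would therefore exist for participants who never had Stop-Cannabis, and it cannot distinguish patterns of use within that app. Second, adherence to Stop-Cannabis is named in a primary outcome but has no metric that this app can generate. The article's closing research implications say the study should help decide whether a randomised trial of an intervention based on Stop-Cannabis could be run, and adherence to that app bears directly on the decision.

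**Working it through.** The plan gives no figure to reproduce and no arithmetic applies. The check compares what each app is said to produce with what the outcome and analysis sections use.

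1. **What EMA produces.** Fixed and random signals, plus self-assessments after substance use. Both percentages in analysis (6), and the compliance metric under Primary Outcomes, can be calculated from these.
2. **What Stop-Cannabis produces.** Counts of openings and counts of views or uses of each element. Its push messages are motivational. No random prompt and no daily assessment schedule is described, so a percentage of random prompts cannot be formed. Users do complete profile assessments and update their current use, but no expected frequency is stated, so a percentage of days with an assessment completed has no defined denominator either.
3. **What the primary adherence outcome uses.** Only prompt and predetermined-assessment completion, which is an EMA quantity.
4. **What the stated expectations cover.** The Sample Size section expects good compliance with both apps. The numerical compliance expectations under Anticipated Results (more than 70% of random signals, 50% of end-of-day assessments, 40% of both) all refer to EMA. The dropout limits in Statistical Methods (less than 40% at 6 months, less than 50% at 12 months) are stated for EMA and the traditional method.
5. **What analysis (6) uses.** Two EMA quantities under a label that names both apps, with no stated restriction to participants given Stop-Cannabis.
6. **Where the Stop-Cannabis log is used.** The text says "The app will automatically monitor the number of times each participant opens the app", but no outcome or statistical section names these counts.

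Two mismatches follow. Objective 6 asks about Stop-Cannabis, while its defined exposure is EMA completion. The primary outcome asks about adherence to two apps, while its metric fits one.

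**The case against.** The strongest reply is that the article collects what is needed. Openings and element use are logged automatically, and the per-element counts suit the question about patterns of use. Deriving variables from a described log is commonly left to the full protocol or the SAP, which are not shown. On that view the fault is a loosely worded parenthesis covering two apps at once.

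Part of this stands. A reader might infer that Stop-Cannabis use goes unmeasured; the documents do not support that. Use is logged, satisfaction questionnaires for both apps are planned at 6 months and 1 year, and dropout, usability and interviews with 10 participants address acceptability.

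A reader might also infer that a claim of benefit will rest on the wrong app's data. That too goes further than the text. The Anticipated Results section calls analysis (6) exploratory and preliminary, and the Limitations section says no firm conclusion on the benefit of Stop-Cannabis can be drawn.

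The appeal to an unseen SAP does not remove the point. The article does not leave the exposure open; it fixes one, and that one does not fit the named app. A SAP written faithfully from this text would carry the mismatch forward.

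**Conclusion.** The point holds in this form: app use and compliance are defined only by EMA prompt and assessment completion, and the Stop-Cannabis log is tied to no stated outcome or analysis. As written, objective 6 is tested with the wrong exposure, and the Stop-Cannabis part of the primary adherence outcome lacks a fitting measure.

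The size cannot be given as a number. The distortion in analysis (6) depends on how closely EMA completion tracks Stop-Cannabis use and on whether both share causes with the outcome, such as motivation or severity; the documents say nothing on either. The observed correlation could differ from the intended one in either direction.

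The conclusion assumes that Stop-Cannabis sends no scheduled or random assessment prompts beyond what the article describes. Since analysis (6) is exploratory and the underlying data are already planned, this is a moderate correction. The gap in the primary adherence outcome carries more weight than the one in analysis (6).

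**What to change.** - **Statistical Methods, Secondary Outcomes (6).** Keep the two completion percentages for EMA only. For Stop-Cannabis, use the logged number of openings as the level of use and the logged counts for each element as the pattern of use. Restrict this analysis to participants given Stop-Cannabis.
- **Outcomes, Primary Outcomes.** Name the same logged counts as the Stop-Cannabis adherence measure, and report it separately from EMA compliance.
- **Time-based summaries.** Use measures such as active days only if the log records dates; the article describes counts alone, so this should be confirmed first.

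The cost is a change of wording and a few variables derived from counts already due to be collected. No further participants, visits or procedures are needed.

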#### Calendar

March 2016: training the medical team to use the screening tools (i.e., DEP-ADO).December 2016: start of participant inclusion (t0).December 2017: end of data collection for participants enrolled at t0.November 2018: end of inclusion.December 2018 to January 2019: start of analysis of baseline data, i.e., prevalence of SUDs.November 2019: end of data collection for final participants included.December 2019 to January 2020: analysis of final data.February 2020: preparation of an abstract for submission to psychiatric congress.April 2020: writing one to three articles for psychiatric and addiction journals.

## Discussion

### Anticipated Results

#### Primary Objectives

A degree of correlation higher than 0.70 is expected between EMA data and data collected using other methods (particularly frequency of use), in line with prior studies (46). EMA should lead to predictions regarding the course of SUDs over the 1-year follow-up (e.g., in term of persistence, severity, and functional impairment) at least as good as other methods; that would be of interest for the clinicians involved in usual care. A high level of compliance with EMA is expected, despite the relative severity of the study sample. Based on previous studies in adolescents (45, 67), participants are expected to complete a mean of more than 70% of random signals, 50% of end-of-day assessments, and 40% of both random and end-of-day assessments. Indeed, there is good evidence that EMA can be used by patients with severe psychiatric disorders (e.g., schizophrenia) or cognitive difficulties (32, 46).

#### Secondary Objectives

This study will measure the prevalence and the characteristics associated with the presence of SUDs in a sample of adolescents hospitalized in a psychiatric setting. Findings are expected to be in a similar range as those previously reported by Daudin et al. (18). We will then examine the possible relationship between SUDs and specific psychosocial and clinical features of inpatient adolescents. We expect this study to confirm that both internalized and externalized disorders are significantly associated with SUDs and that the presence of SUDs is associated with a higher level of impulsivity, mood dysregulation/borderline traits, and sensation-seeking traits (68–70). We predict that a bidirectional positive relationship between the level of substance use and the severity of other psychiatric symptoms will be noted at a daily level, and – if confirmed – that this association would be strengthened in a context of interpersonal relationship (with family and with peers) compared to other situations. A significant negative association between the level of the Stop-Cannabis app use and the participant’s clinical outcome at follow-up is expected. Such additional exploratory analysis would provide preliminary information about the possible benefit of the app in naturalistic settings.

### Limitations

Several limitations may preclude interpretation of our findings. As no control group for the Stop-Cannabis app is defined (i.e., subjects with cannabis use disorders without the intervention), the effectiveness of the Stop-Cannabis app to reduce or quit cannabis cannot be directly examined in our study. Furthermore, one other limitation is related to the lack of EMA assessments for the control group. The groups cannot be then compared with the EMA data. The authors choose to not use EMA assessment for the control group in order to avoid possible impact of the assessments on the behaviors [for a discussion about the reactivity effect of EMA, see Shiffman (25)]. The groups will receive, however at different time, a number of clinical assessments useful for the planned comparisons. As our study participants will be recruited during hospitalization in a university teaching hospital, the sample is likely to comprise youths with severe or resistant clinical profiles, which could limit the generalizability of our findings. In addition, the study design requires that only participants who own a smartphone are included, which is a risk for selection bias. Attrition biases may result from high dropout rates and low use of the app, but incentives and reminder phone calls will be employed to improve adherence. However, if important differences in baseline characteristics between adherent and non-adherent participants are detected, this will be further controlled by regression analyses. Finally, no firm conclusion about the benefit of the Stop-Cannabis application can be drawn from this study with regards to the lack of controlled randomized group.

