## Methods and Analysis

### Selection of Participants

#### Inclusion and Exclusion Criteria

Participants will be adolescents (11–18 years old) who are hospitalized in the Department of Child and Adolescent Psychiatry at the Pitié-Salpêtrière University Hospital between September 2016 and September 2018. The participants will be assessed at baseline. According to the presence or absence of comorbid SUDs, they will be included in either the SUDs group or the control group. The SUDs group will receive the mobile apps, whereas the control group will not. Exclusive tobacco consumption is not considered to be a criterion for inclusion in the SUDs group. Inclusion to the non-SUD control group will be made according to a match with adolescents from the SUDs group (for age, gender, inpatient unit, and time of admission). Exclusion criteria include non-French speaking, those without a personal mobile phone, lack of informed consent from parents or from the adolescents, and any mental or physical problems that interfere with participation in the study (e.g., autism with very low communication abilities, severe to profound intellectual disability, severe motor disability).

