#### Sample Size

A conservative approach was adopted for this feasibility study, which emphasizes descriptive and qualitative feedback. Consequently, based on the recommendations for pilot studies (44), we plan to include 80 participants (40 cases, 40 controls) over a 2-year inclusion period. As there are around 280 inpatient admissions per year in the Department of Child and Adolescent Psychiatry, i.e., *n* = 560 potential participants contacted at baseline during the 2 years, this will represent a 14% inclusion rate. We predict that the prevalence of SUDs will be similar to that previously reported (18). A good level of compliance with EMA and Stop-Cannabis is expected, consistent with previous studies that reported high levels of adherence (up to 80%) to similar tools in adolescents with comorbid psychiatric disorders (31, 45), and in adults with associated severe psychiatric disorders (32, 46). An acceptance rate of 80% is expected in the SUD group and 50% for the control group. A 50% retention rate at 1-year follow-up is anticipated based on previous longitudinal studies among adolescents (47). In case of a lower enrollment rate, we will either continue to enroll participants during an additional year (2019) in order to reach the intended sample size or use incentives (e.g., free participation in leisure and sport activities in groups) to encourage participant enrollment.

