#### Statistical Methods

##### Primary Outcomes

Pearson correlations will be used to determine the strength of associations between daily substance use assessed by either EMA, or self-report questionnaire (e.g., CAST), or by clinician-report questionnaire (e.g., RECAP) during the clinical assessment at 6 months. Clinical reliability of the EMA will be endorsed if the correlations are statistically significantly higher than 0.70. Further analyses would be performed to estimate different aspects of reliability of the data collected in line with Perrez et al. (64). The severity of SUDs at baseline should predict the severity of substance use and the level of functional impairment at 1 year at least to comparable levels while using EMA data at baseline compared with traditional methods. Two simple linear regression models will be performed. For both the models, the dependent variable will be the severity of SUDs at follow-up; in one model, the independent variable will be the severity of SUDs based on EMA data (Model A), whereas in the other model, the variable will be severity of SUDs based on self- and clinician-report (Model B). The estimate of the independent variable is expected not to be lower in the Model A than in the Model B.

The dropout rate is expected to be less than 40% at 6 months and less than 50% at 12 months for both the EMA and traditional method, with no significant difference between methods. The results of the satisfaction survey will be estimated by analyzing the percentage of answers and the differences among the different categories using Chi-square analysis.

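### Adjustment for attrition and low adherence depends on an undefined, data-dependent trigger, while the default 1-year analyses are unadjusted

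*Protocol article*

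**What the plan says.** The Limitations section recognises that dropout and low app use may bias the findings. It offers incentives and reminder calls to improve adherence, and then one analytic response: "if important differences in baseline characteristics between adherent and non-adherent participants are detected, this will be further controlled by regression analyses". No test, threshold, size of difference or covariate is named.

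The numbers it would work on come from three places:

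- Sample Size: "we plan to include 80 participants (40 cases, 40 controls) over a 2-year inclusion period", and "A 50% retention rate at 1-year follow-up is anticipated".
- Inclusion and Exclusion Criteria: "The SUDs group will receive the mobile apps, whereas the control group will not".
- Statistical Methods, Primary Outcomes: "The dropout rate is expected to be less than 40% at 6 months and less than 50% at 12 months".

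The default 1-year analyses carry no adjustment. Under Statistical Methods, Models A and B are regressions with one predictor each. Onset and persistence of substance use disorder (SUD) are examined by univariate logistic regression, and app use against clinical outcome by correlation. The only significance level stated, 0.05, belongs to secondary outcome 2, the comparison of participants with and without SUD.

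**The concern.** Making adjustment conditional on a preliminary comparison has two weaknesses. In a small sample the comparison may not flag a difference large enough to matter, and the analysis then stays unadjusted. And the choice of model comes to depend on the data, so the reported estimate is the product of an unstated selection step.

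Most is at stake in secondary outcome 6. There the extent of app use is the exposure, and frequency of use and functional impairment at 1 year are the outcomes. Baseline severity could plausibly drive both. The section on anticipated results expects a significant negative association there, and the section on clinical and research implications says the study will help decide whether a randomised trial of Stop-Cannabis could be conducted. An association that partly reflects who was less severely ill at discharge would mislead that decision.

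**Working it through.** **The plan's own figure.** The sample size is set by a recommendation for pilot studies, so there is no power calculation to reproduce. The linked arithmetic does reproduce: 280 × 2 = 560 admissions, and 80/560 = 14.3%, stated as 14%.

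**Group sizes.** App adherence is defined only in the 40 SUD participants. The protocol does not define adherent, so several splits are shown:

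- 50% retention at 1 year: 20 versus 20.
- 40% dropout at 6 months: 24 versus 16.
- 80% adherence: 32 versus 8. This takes the Sample Size remark that earlier studies "reported high levels of adherence (up to 80%) to similar tools" as a share of participants, which is an assumption.
- Dropout pooled over all 80 at 50%: 40 versus 40.

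**Power, if detected means p < 0.05 two-sided.** Both that criterion and the sizes of difference are assumptions. For a difference of d standard deviations, the noncentrality is d × √(n1·n2/(n1+n2)), referred to a noncentral t with n1+n2−2 degrees of freedom. At d = 0.5:

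- 20 versus 20: 0.5 × √10 = 1.58
- 24 versus 16: 0.5 × √9.6 = 1.55
- 32 versus 8: 0.5 × √6.4 = 1.26
- 40 versus 40: 0.5 × √20 = 2.24

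| Split | d = 0.3 | d = 0.5 | d = 0.8 | d detectable at 80% power |
|---|---|---|---|---|
| 20 vs 20 | 15% | 34% | 69% | 0.91 |
| 24 vs 16 | 15% | 33% | 68% | 0.93 |
| 32 vs 8 | 12% | 23% | 51% | 1.14 |
| 40 vs 40 (all 80) | 26% | 60% | 94% | 0.63 |

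For a binary characteristic at 50% versus 70%, power is 25% (20 versus 20), 16% (32 versus 8) and 45% (40 versus 40).

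**Effect on the estimate.** A simulation of 8,000 runs assumed one baseline covariate differing by 0.5 SD between adherent and non-adherent participants, a slope of 0.5 on the outcome (correlation about 0.5), no true effect of adherence, and outcomes observed in everyone. The expected unadjusted bias is 0.5 × 0.5 = 0.25 SD.

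| Split | Unadjusted | Adjust only if p < 0.05 | Always adjust |
|---|---|---|---|
| 20 vs 20: bias (SD) | 0.25 | 0.11 | 0.00 |
| 32 vs 8: bias (SD) | 0.25 | 0.13 | 0.00 |
| 20 vs 20: false-positive rate | 12.2% | 5.9% | 5.3% |
| 32 vs 8: false-positive rate | 9.3% | 5.6% | 5.4% |

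The conditional rule leaves roughly half the bias (0.11/0.25 = 44%; 0.126/0.246 = 51%). Its false-positive rate stays near 5%, so the damage in this setting is to the size of the estimate rather than to the test.

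**The case against.** The strongest reply is that the protocol names no test. An important difference can be read as a judgement of size, which suits a study that says it emphasises description, and on that reading the power figures do not apply. This stands as a limit on the figures. It does not rescue the rule: with no size given, the decision to adjust is then a judgement made with the data in view.

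A reader might infer that the rule will usually miss important differences and that every 1-year result is therefore biased. The documents do not support that, for four reasons:

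- The protocol sets no size for important. At 0.8 SD, detection in the SUD group is 51–69%, and over all 80 it is 94%.
- The rule covers baseline characteristics in the plural. If three independent measures each differed by 0.5 SD, at least one would be flagged 1 − 0.662³ = 71% of the time with 20 versus 20. Correlated measures would fall between 34% and 71%.
- Several outcomes are not exposed in this way. Dropout is itself an outcome, compliance is counted from prompts, and the validity correlation is taken at 6 months.
- The protocol does not say that the 1-year analyses are complete-case. It plans mixed-effects models for the EMA data, and handling of missing data may be set out in a plan not shown.

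It is also fair that this is one sentence in the Limitations of a pilot study, which already disclaims firm conclusions on the app's benefit. That lowers the stakes, but the sentence still states a rule, and a better one is available from data already collected.

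**Conclusion.** The concern holds in a limited form. The protocol makes adjustment depend on an undefined trigger, and the stated 1-year default is unadjusted. Under either reading the trigger is a poor choice: as a significance test it would find a 0.5 SD difference among the app users only about 23–34% of the time, and as a judgement of size it is a choice made after seeing the data.

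The percentages rest on p < 0.05 two-sided, a single covariate, and assumed splits and effect sizes. The pooled dropout comparison does better, at about 60% for 0.5 SD. The bias figures rest on the simulation's assumed slope and full follow-up; with half the group lost, the real analysis would be smaller and less certain. The change is worth making, chiefly for secondary outcome 6.

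**What to change.** 1. Remove the conditional sentence as a rule for choosing the model.
2. In the analysis of app use against 1-year outcome, always adjust for the baseline value of that outcome: RECAP frequency of use for substance use, C-GAF for functioning. In practice this is a partial correlation or a linear regression with one added term. With about 20 SUD participants retained (50% of 40), use one covariate, two at most.
3. Report standardised baseline differences between adherent and non-adherent participants, and between those retained and those lost, as description only. Define adherent when doing so.
4. Do not add baseline use to Models A and B. Model B's predictor already is self- and clinician-reported severity, and in Model A the addition would adjust EMA severity for the measure it is compared with. For these models, and for the univariate logistic models, which cannot carry several forced covariates, add one sensitivity analysis of all enrolled participants, by retention weights or by multiple imputation from baseline and 6-month data.

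RECAP and C-GAF are already scheduled at baseline, 6 months and 1 year in Table 1, so no new data are needed. The cost is a degree of freedom or two, possibly a slightly less precise estimate, and a little more analysis. None of this deals with dropout driven by factors that were not measured, and the report should say so.
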